More than 40 years of research demonstrates that parenting interventions based on social learning theory are effective in decreasing coercive parenting, increasing positive parenting and, in turn, improving child externalising problems [13–16]. Parenting interventions are effective in the short-term and longer-term, with positive effects on child outcomes lasting up to 20 years post-intervention [17]. Parenting interventions can be offered as universal interventions for all parents, or as targeted interventions for more at-risk children and families. Despite the effectiveness of both universal and targeted interventions, research has found that few parents participate in face-to-face parenting interventions and many drop out early. In a recent meta-analytic review of targeted parenting interventions (*k* = 262), Chacko et al. [18] found that at least 25% of parents of children with externalising problems dropped out prior to commencement and 26% dropped out during treatment. Similarly, participation rates are also low in universal parenting interventions. For example, in a randomised controlled trial (RCT) of a universal parenting intervention in Germany, only 31% of the population participated [19]. While there are a number of reasons for low participation rates and high attrition, the practical demands of participation (e.g., time, work, child care, transportation and costs) are likely to be key barriers to participation in traditional face-to-face parenting interventions for many families [20].

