### Participants

Eligible participants will be Australian parents or caregivers of children aged 2–16 years. We aim to recruit 1200 parents/caregivers to participate in the study. To be eligible for the study, participants must be: a parent or caregiver of a child aged 2–16 years; aged 18 and over; currently living in Australia; and able to complete the questionnaires and understand the program content in English. The ParentWorks website will be geoblocked so that only participants located in Australia will be able to register for, and participate in, the program.

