### Recruitment of study population

A national media campaign will be conducted to promote ParentWorks through online and social media channels, as well as traditional media formats, such as radio. In order to achieve high rates of father participation, the media campaign will include short videos of fathers talking about the challenges of parenting, and will prompt parents to participate in ParentWorks. In addition to the media campaign, potential participants may also hear about the program through word of mouth, flyers distributed through child and family services, and practitioner recommendations. Interested participants will be directed to the program website for more information and to enrol in the program. While the program website will be specifically developed to be appealing for fathers/male caregivers, mothers will also be encouraged to complete the program, and two-parent families will be encouraged to complete the program together.

Potential participants can watch an introductory video about the program on the ParentWorks website. If they elect to participate in the program, they will be required to read the participant information statement and indicate consent to the conditions listed in the online consent form. As the program will be delivered online, participants will not provide written consent, but will indicate their consent to participate by clicking a box acknowledging that they have read the information statement and they agree to participate. They will then register for the program by completing a series of questions in an online registration form. The questionnaires will be anonymous and no identifying information will be obtained. There will be a separate registration for each parent/caregiver (for two-parent families), and each parent will complete questionnaires independently throughout the program. The parent who initially registers for the program is encouraged to discuss program participation with their partner/co-parent before making a decision about whether to participate in the program with or without their partner/co-parent. See Fig. 1 for a flowchart of participant recruitment and progression through the program.

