### Sample size

The sample size calculation was conducted with G*Power [46]. To detect a small effect of ParentWorks on the primary measure of child outcomes (SDQ; Goodman, 2007) with *d* = 0.2 and 0.8 power, a final sample size of 800 two-parent families is required. Of these families, we expect that approximately 400 fathers will elect to participate. In order to account for attrition rates, and participation of single-parent families, we aim to recruit at least 1200 families. This sample size will also be sufficient to conduct the analyses examining level of father involvement, predictors, moderators, and mediators. There are no plans to carry out interim analyses.

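### The recruitment target is 1200 parents in one section and 1200 families in another; counted in parents it leaves no allowance for loss, counted in families it reaches 800 only under rates the protocol does not state

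*Protocol article*

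**What the plan says.** The Participants section of the protocol article sets the target in individuals: "We aim to recruit 1200 parents/caregivers to participate in the study". The Sample size section sets it in families: "In order to account for attrition rates, and participation of single-parent families, we aim to recruit at least 1200 families".

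The Sample size section derives its requirement from d = "0.2 and 0.8 power" and concludes that "a final sample size of 800 two-parent families is required". It adds: "Of these families, we expect that approximately 400 fathers will elect to participate". It names the software ("The sample size calculation was conducted with G*Power") but gives no alpha, no attrition rate and no single-parent share.

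The section Recruitment of study population makes parents and families separate counts, since the two parents of a family enrol individually and fill in their own questionnaires.

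The only numerical dropout rates in the article are in the Background, from a meta-analytic review of targeted interventions: "at least 25% of parents of children with externalising problems dropped out prior to commencement and 26% dropped out during treatment".

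**The concern.** The same number, 1200, is attached to two units that differ by several hundred participants. A team that counts registered parents and one that counts families would consider recruitment complete at different points, and both could cite the protocol.

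At stake is whether the recruitment target supports the stated final sample and power. The Sample size section also relies on this sample for the analyses of father involvement, predictors, moderators and mediators, and no interim analysis is planned that might reveal a shortfall.

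**Working it through.** **Inputs.** From Sample size: d = 0.2, power 0.80, final N of 800 two-parent families, about 400 fathers among them, 1200 families. From Participants: 1200 parents. From the Background: 25% lost before commencement, 26% lost during treatment. Assumed, because not stated: alpha 0.05 two-sided; single-parent share s from 0 to 30%; one other parent taking part in each two-parent family, so 1 + 400/800 = 1.5 registered parents per two-parent family.

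**Step 1: reproduce the 800.** For two independent equal groups, n per group = 2(1.960 + 0.842)²/0.2² ≈ 393, or 786 in total (788 with the noncentral t). Groups of 400 and 400 give power 0.81. The 800 is therefore consistent with a two-group comparison. A one-sided test would need 620 in total and a paired pre-post test 199, so neither matches. The power figures below use the equal two-group comparison: power = Φ(0.2·√(N/4) − 1.960).

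**Step 2: compare the two targets.** 1200 families would register 1200 × [s + 1.5(1 − s)] parents: 1800 at s = 0 and 1620 at s = 30%. Neither is 1200.

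**Step 3: the target counted in parents.** 800 + 400 = 1200, so the required final sample takes up the whole target. In general the number of two-parent families recruited is (1 − s) × 1200/[s + 1.5(1 − s)].

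| Single-parent share (assumed) | Two-parent families recruited | After 26% loss | After both losses (0.75 × 0.74 = 0.555 retained) |
|---|---|---|---|
| 0% | 800 | 592 | 444 |
| 10% | 745 | 551 | 413 |
| 20% | 686 | 507 | 381 |
| 30% | 622 | 460 | 345 |

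Power is about 0.68 at 592 families and 0.56 at 444. At 1.5 parents per two-parent family, any attrition at all leaves fewer than 800.

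**Step 4: the target counted in families.** Two-parent share × retention must be at least 800/1200 = 66.7%. Final two-parent families = 1200 × (1 − s) × retention, with power in brackets:

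| Single-parent share (assumed) | 26% loss only | Both losses |
|---|---|---|
| 0% | 888 (0.85) | 666 (0.73) |
| 10% | 799 (0.81) | 599 (0.69) |
| 20% | 710 (0.76) | 533 (0.64) |
| 30% | 622 (0.70) | 466 (0.58) |

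With 26% loss alone, the break-even single-parent share is 1 − 800/(0.74 × 1200) = 9.9%. With both losses, 800 is not reached even at s = 0; that would need 800/0.555 ≈ 1442 families.

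**The case against.** A reader might infer that the target fails in either unit. The documents do not support that for families. The Background rates come from targeted interventions, in a passage about face-to-face delivery; this trial is universal, online and self-paced, and the article argues that online delivery lowers the practical burden. The Sample size section does not adopt either rate. If a family counts as recruited once it has started, only the 26% would apply, and 1200 families would give 888 with no single-parent families. This part of the objection stands: a loss of one third from 1200 to 800 is internally possible.

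A reader might also want a single restated sample size. Any such figure needs a single-parent share that the article does not give, so only a range is defensible. Nor can recovery of power through adjustment for baseline SDQ be promised: it depends on a pre-post correlation that is not given, and father participation is self-selected.

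Two further points limit the consequence. The article says it powers an effect of ParentWorks on the SDQ. If d = 0.2 were a standardised paired change, 199 families would suffice, so the pre-post question stays well powered at the yields in Step 3; the loss of power concerns a two-group contrast such as father participation. And the Participants section states an aim, not a cap.

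Finally, an article may leave attrition assumptions to a fuller document. But no such document can make both published targets true. If each two-parent family supplied only one parent, the two counts would coincide, but that contradicts the expected 400 fathers alongside mothers who rate the child.

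**Conclusion.** The contradiction in units is established from the text alone. Counted in parents, the target cannot deliver 800 final two-parent families once there is any attrition or any single-parent family. This rests on about half of fathers joining a participating partner, as the article expects. A 26% loss, used only as an illustration, would leave about 592 families and power of about 0.68 instead of 0.80.

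Counted in families, adequacy is conditional. The target works if two-parent share times retention is at least 66.7%. It is met at 26% loss with up to about 10% single-parent families, and missed if both cited losses apply (at most 666 families, power about 0.73). The article does not say which case it planned for. All power figures assume d = 0.2, an equal split and two-sided alpha of 0.05.

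**What to change.** Use families as the recruitment unit in both the Participants and Sample size sections, and if a number of parents is also wanted, give it as a separate, derived figure. In Sample size, state the attrition rate and single-parent share that lead from 1200 to 800, and say whether a family counts as recruited at registration or on starting the program. Then restate the expected final number of two-parent families and its power under those assumptions, as a range if they are uncertain.

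This takes a few sentences. The correction adds no participants; the only cost is that the stated final number and power may be less favourable.

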### Reporting of results

Reporting of the trial will follow the TREND statement for behavioural and public health interventions involving non-randomised designs [47]. The overall trial results will be communicated through presentations at national and international conferences, and articles in peer-reviewed scientific journals. It is a requirement of the trial funding body that the results are reported in open-access, peer-reviewed publications.

## Discussion

Online parenting interventions have the potential to address many of the practical barriers to participation in traditional face-to-face interventions, especially for fathers. Currently, fathers are significantly underrepresented in research on evidence-based parenting interventions, including those delivered online. Thus, the online parenting intervention described in the present study protocol is specifically developed to meet the needs and preferences of fathers, as well as mothers. By considering fathers’ needs and preferences in regard to program content, and targeting the intervention to fathers as well as mothers, it is expected that both father engagement and the effectiveness of the intervention will be maximised. This study has a number of additional strengths. Firstly, by collecting and evaluating data from all participating parents, it will contribute valuable information about intervention effectiveness using both mothers’ and fathers’ ratings of parenting and child behaviour, and will allow for the investigation of any additional benefits due to father participation. Secondly, this will be one of only a few studies conducted to examine a universal online parenting intervention provided without any practitioner support, and will thus add to the evidence base about the effectiveness of self-directed interventions. Third, the inclusion of a three-month follow-up evaluation will allow for examination of whether changes in child behaviour and parenting are maintained over time. Finally, this study will use a large-scale media campaign to support the recruitment of a large sample size, which has not yet been achieved in similar research to date.

Despite these strengths, the use of a single group repeated measures design is a methodological weakness, which results in the inability to control for potential confounds, such as maturation effects in children. However, given that this study involves dissemination of a universal parenting intervention, with recruitment supported by a national media campaign, it would not be feasible to implement it as part of a randomised controlled trial. While this design limitation will temper conclusions regarding the effectiveness of the intervention, the strengths of this study have the potential to contribute significant knowledge and inform public policy about enhancing the engagement of fathers in parenting interventions, implementing universal online parenting interventions, and establishing a national approach to reducing child externalising problems.

## Abbreviations

ADHD: Attention deficit hyperactivity disorder
CD: Conduct disorder
DBD: Disruptive behaviour disorder
ODD: Oppositional defiant disorder
PAFAS: Parenting and family adjustment scales
PPC: Parent problem checklist
SDQ: Strengths and difficulties questionnaire
